**Table 2.4 Characteristics of Intervention**

| Study               | Duration of intervention               | Mode of Delivery                                                        | Content                                                                                                                                                                                                                                                                                                                                                                         | Control    |
|----------------------------|-----------------------------------------------|--------------------------------------------------------------------------------|----------------------------------------------------------------------------------------------------------------------------------------------------------------------------------------------------------------------------------------------------------------------------------------------------------------------------------------------------------------------------------------|-------------------|
| Skre et al., 2013   | 3 days                                        | Talk                                                                           | 
 
1. Information about the clinical picture
 
2. Epidemiology
 
3. Treatment of anxiety, depression, eating disorders, and schizophrenia
 
4. Available help system.
 
                                                                                                                                              | Not mentioned     |
| Milin et al., 2016  | 2 weeks                                       | Digital stories, video interview                                               | 
Curriculum Guide (6 modules)
 
 
1. Stigma reduction through digital stories and video interview of youth with mental illness
 
2. Understanding of mental health and brain functions
 
3. Mental illnesses and treatment
 
4. Help-seeking behaviors and mental health self-help competencies
 
               | Teaching as usual |
| Swartz et al., 2017 | 3 hours given in 2-3 periods                  | Interactive lectures, videos, film assignments, homework, and group activities | 
 
1. Identifying symptoms of depression
 
2. Understanding the process of medical decision-making
 
3. Seeing parallels between depression and other medical illnesses
 
4. Recognizing suicide as a potential consequence of depression
 
5. Understanding that depression is a treatable medical illness
 
 | Waitlist          |
| Campos et al., 2018 | Two sessions, 90 mins each, one-week interval | Group dynamics, music, and videos.                                             | 
 
1. Risk factors for mental health
 
2. Symptoms and signs of five mental disorders
 
3. Promotion of nonstigmatized behaviors towards mental disorders
 
                                                                                                                                                                 | Not mentioned     |

|                                   |               |                                                                       |                                                                                                                                                                                                                                                                                                                                     |                                                                                        |
|-----------------------------------|---------------|-----------------------------------------------------------------------|-------------------------------------------------------------------------------------------------------------------------------------------------------------------------------------------------------------------------------------------------------------------------------------------------------------------------------------|----------------------------------------------------------------------------------------|
|                                   |               |                                                                       | 4. Impact of mental health
5. Formal and informal help-seeking options
6. Promote first aid skills towards people with a mental health problem
7. Self-help strategies and explore mental health-promoting behavior.                                                                                                       |                                                                                        |
| Yamaguchi et al., 2020     | 50 minutes    | Animated video, discussion                                            | 1. Mental disorders being common,
2. Mental health problems being closely associated with lifestyle, including sleep habits
3. Seeking help from reliable adults being a key to solving the problems
4. Knowledge about the symptoms of severe mental illnesses
4. Skills to support peers with mental health problems. | Waitlist                                                                               |
| Ibrahim et al., 2020       | Not mentioned | Small group activities, explanatory talk, animation video.            | 1. Information on mental health and depression
2. Facts on mental health statistics                                                                                                                                                                                                                                              | Not mentioned                                                                          |
| Taylor Rodger et al., 2014 | 3 weeks       |                                                                       | Psychoeducation
1. Vignette of a typical young person experiencing a mental health problem
2. Description and symptoms
3. Challenging stigmatizing views
4. Treatment and help options                                                                                                                                  | Link to webpages on dental hygiene, common household medications, and nutrition facts. |
| Reavley et al., 2014       | Not mentioned | Website/ Facebook pages, Twitter activities, emails, booklet, posters | 1. Depression and related disorders are common in young people
2. There are recognizable signs of depression and related disorders in young people
3. Early help-seeking leads to better outcomes                                                                                                                             | Not mentioned                                                                          |

|                        |         |                    |                                                                                                                                                                                                                                                                                                                                                                                                                                                                                                                                              |            |
|------------------------|---------|--------------------|----------------------------------------------------------------------------------------------------------------------------------------------------------------------------------------------------------------------------------------------------------------------------------------------------------------------------------------------------------------------------------------------------------------------------------------------------------------------------------------------------------------------------------------------|------------|
|                        |         |                    | 4. There are several sources of professional help available
5. There are useful types of self-help available
6. There are helpful first aid actions that staff and peers can take.                                                                                                                                                                                                                                                                                                                                                     |            |
| Li et al., 2013 | 3 weeks | Website videogames | “Ching Ching story” (10 topics)
1. Identifying stressors and how to handle stress
2. Understanding the relationship between stress and coping, and the consequence of depression
3. Understanding what goal-directed thinking
4. Affirming existing strengths and acknowledging the concept of “self”
5. Cognitive restructuring
6. Advance cognitive restructuring
7. Understanding others’ feelings
8. Communication skills
9. Conflict resolution based on a problem -solving approach
10. Anger management | No control |

**Table 2.5 Outcome Measure and Outcome**

| Outcome Measure            |                                                                                                                                             | Mental Health Literacy                                                 | Help-Seeking                          |
|-----------------------------------|---------------------------------------------------------------------------------------------------------------------------------------------|-------------------------------------------------------------------------------|----------------------------------------------|
| Skre et al., 2013          | Developed questionnaire on symptom profile recognition, prejudiced belief and knowledge about where to seek help for mental health problems | I- MD 0.27 (0.24-0.30, $p<0.001$
C- MD 0.00 (-0.03, 0.03), $p=0.92$        | Not measured                                 |
| Milin et al., 2016         | Developed questionnaire for mental health knowledge and attitude towards mental illness                                                     | I- $F_{1,521.74} = 20.09$ , $p<0.001$
C- $F_{1,484.28} = 0.55$ , $p=0.459$ | Not measured                                 |
| Swartz et al., 2017        | Developed questionnaire on adolescent depression knowledge and reported and intended behaviour scale                                        | I- aOR 3.10 (2.0,5.0), $p<0.001$                                              | Not measured                                 |
| Campos et al., 2018        | Developed MHLq                                                                                                                              | 5.693 (4.682, 6.704)                                                          | 0.744 (0.133, 1.356)                         |
| Yamaguchi et al., 2020     | Developed questionnaire on general knowledge about mental health and illness and vignettes                                                  | MD 3.92 (3.63, 4.22)                                                          | OR=6.32 (3.45,11.74)                         |
| Ibrahim et al., 2020       | D-lit and MHSAS                                                                                                                             | $F_{(2,84)} = 13.266$ , $p<0.001$
MD 3.233                                 | $F_{(2,84)} = 9.939$ , $p<0.001$
MD 6.535 |
| Taylor Rodger et al., 2014 | A-Lit, D-Lit, Attitude Toward Seeking Professional Help Short Form Scale General Help-Seeking Questionnaire                                 | Depression literacy- 1.11, $p=0.131$
Anxiety literacy- 3.00, $p<0.001$     | 3.46, $p= 0.009$                             |
| Reavley et al., 2014       | Developed scale based on Vignette                                                                                                           | 1.56 (0.73-3.33)                                                              | 1.42 (0.58-3.46)                             |
| Li et al., 2013            | Developed 31 item questionnaires                                                                                                            | 2.2 (3.66), $p<0.001$                                                         | Not measured                                 |

Abbreviation: MHLq- Mental Health Literacy Questionnaire, D-Lit- Depression Literacy scale, MHSAS- Mental Help Seeking Attitude, A-Lit- Anxiety Literature Scale. MD- Mean Difference, aOR- adjusted Odds Ratio.

### **2.11.5 Summary of Review on Interventions**

This review examined the available evidence of health education intervention on mental health literacy and help-seeking behaviour among young people. Nine published studies were identified and included. This review found that most of the studies reported significant improvement in mental health literacy among young people after health education intervention. Out of five studies that assessed the effect on help-seeking behaviour, only two studies reported a significant effect in improving help-seeking behaviour. The findings are similar to previous studies that reported health education interventions only increase mental health literacy, but not help-seeking behaviour (Kauer, Mangan, & Sanci, 2014; Tay et al., 2018).

There are various settings for interventions to improve mental health literacy among young people. This includes whole-of-community interventions, community interventions targeted at young people, school-based interventions, and online-based interventions (Kelly et al., 2007). This review found that most of the health education interventions for young people were conducted in the school setting. The interventions were led by teachers and incorporated into the school curriculum. The school has been shown to be effective as a medium to deliver health education intervention and teachers have emerged as the key (Weare & Nind, 2011). Teachers are an important resource in the implementation of the program, as they already have knowledge and rapport with the children and can adapt to their culture. Furthermore, incorporating the program with the curriculum will ensure the program's sustainability. However, previous reviews reported inconclusive findings on the effect of a mental health intervention in school (Metrics, 2017; Salerno, 2017; Webelhorst et al., 2020; Wei et al., 2013).

Only a few of the studies were conducted by leveraging technology. Technology has become a part of everyday lives, with youth age 15-24 as the most connected age group. It was reported that 80% of the adolescents possess mobile phones and one in three are internet users

(UNICEF, 2017). Digital health intervention is, therefore, appeared to be a promising strategy for health education among young people. It was suggested that promotional healthy behaviors using psycho-education and effective theory-based psychological interventions should be increased by leveraging technology (Murray et al., 2017). Furthermore, young people are more interested in receiving online health promotion for mental illness (Aschbrenner et al., 2019; Do et al., 2019). Interestingly, the studies that were conducted using web-based only included university students. None of the studies were conducted among school students. The previous reviews on digital health education interventions were also mostly focused on adults (Brijnath, Protheroe, Mahtani, Antoniadis, et al., 2016; Xu et al., 2018).

Based on the predictors of help-seeking among young people, strategies to improve help-seeking should focus on improving mental health literacy and reducing stigma (Gulliver et al., 2010). The components of health education intervention should include information on symptoms of mental health problem (such as depression and anxiety), causes of the mental health problem, available mental health services, and treatment available (including pharmacological and non-pharmacological) (Kelly et al., 2007; Okello et al., 2014). The content of the health education intervention in the included studies are the epidemiology of mental illness, sign and symptoms of mental illness, stigma reduction, available treatment and self-help strategies.

Theory of planned behavior constitutes that an individual's intention in a behaviour comes from three factors; namely the attitude toward a behaviour, subjective norms which stem from social influence, and perceived behavioral control. Poor mental health literacy, social stigma, and negative belief towards mental health services and professionals were the most cited predictors for help-seeking behavior. Based on these variables, health education intervention

that aims to increase mental health literacy and reducing stigma appears as promising strategy to promote help-seeking behavior. However, none of the studies developed the intervention based on theory.

In a review of 276 studies, psychoeducation was found to be the most effective intervention in promoting mental health literacy (Salazar de Pablo et al., 2020). A similar finding was reported in a another review (Walters et al., 2020). This is probably because psychoeducational intervention may affect the understanding of depression, symptoms identification, and mental health outcomes (Bevan Jones et al., 2018). However, only one study was reported to give intervention based on psychoeducation (Taylor-Rodgers & Batterham, 2014).

The previous review reported that contents that include active ingredients appear to be more successful (Brijnath, Protheroe, Mahtani, Antoniadis, et al., 2016; Tay, 2018). Similarly, previous reviews reported that a delivery method that includes active ingredients appears to be more successful for young people as it increases engagement (Garrido, Millington, et al., 2019; Liverpool et al., 2020; Seedaket et al., 2020; Tay et al., 2018). Interventions were given either through website, talk, video, game, and discussion.

There was heterogeneity in measuring mental health literacy and help-seeking. Although research on mental health literacy among adolescents is increasing, however, psychometrically tested measures are not well developed (Mansfield et al., 2020; M. O'Connor et al., 2014). A systematic review of mental health literacy tools reported that the Mental Health Literacy Scale (MHLS) and The New Inventory Attitudes Toward Seeking Mental Health Services (IASMHS) have good internal consistency and content validity (Wei et al., 2017).

The review founds that health education intervention to increase mental health literacy among young people are mostly conducted in school setting, and digital intervention were mostly conducted among university students. The mode of intervention should be interactive, and the content follows the mental health literacy framework. It would be recommended for future studies to conduct intervention based on theory and assess the outcome using a psychometric tested measure.

### **2.12 Conceptual Framework**

The independent variable for this study will be the mental health education intervention with the primary outcome of mental health literacy and secondary outcome of help seeking behavior. The intervention will be developed based on the IMB theory. Health education intervention will address the knowledge, motivation and behavioral skills of the theory. Besides the construct of the theory, sociodemographic factors such as gender, ethnicity, and socioeconomic status will be included as it also influences mental health literacy (Lynch et al., 2018; Magaard et al., 2017; Venkataraman et al., 2019). Figure 2.2 below illustrates the conceptual framework using the IMB theory for this study.

[figure not shown]

**Figure 2.2 Conceptual Framework using Information Motivation Behaviour-Skills Model**

## **CHAPTER 3**

### **METHODOLOGY**

This chapter describes the methodology and methods that will be conducted during this study. A detailed explanation that covers the study location, sampling population, sample size, sampling methods, study instrument, intervention program, data analysis strategies, and ethical consideration will be discussed.

#### **3.1 Study Location**

The study will be conducted among foundation students at Universiti Putra Malaysia. The program offers a foundation for ‘Sijil Pelajaran Malaysia’ holders prior to embarking on a degree journey. This foundation program is chosen for the diversity of students enrolled in it, as Malaysian aged 18 and 19 years old, irrespective of ethnicity can apply in the program. The program has two semesters and starts in August every year.

#### **3.2 Study Duration**

The study will be conducted over a period of 24 months, from December 2020 until December 2022. The duration of the study comprised of the planning of the research, development of the health education intervention program, implementation of the program, and evaluation of the program. Data collection will commence in September 2021.

#### **3.3 Study Design**

This study is a randomized controlled trial study with two arms involving intervention and a control group. Foundation students at University Putra Malaysia will be recruited to join the study. They will be explained about the study objectives, activities that will be required to do if agree for participating. Participants who consented to join the study will then be randomized to either the intervention or control group. Baseline measurement will be taken prior to

intervention. The intervention group will be given a theory-based health education intervention via a newly developed website, whereas the control group will be waitlisted. The intervention will be conducted for two weeks. Measurement will be repeated after the intervention (2 weeks) and at follow-up (1 month). The flow diagram of the study conduct based on the CONSORT 2010 statement (Schulz et al., 2010) is shown in Figure 3.1.

[figure not shown]

**Figure 3.1 Flow Diagram of study Conduct based on CONSORT statement.**

### **3.4 Sampling Method**

#### **3.4.1 Study Population**

The study population will be foundation students in Universiti Putra Malaysia that met all inclusion and exclusion criteria.

#### **3.4.2 Sampling Population**

Foundation students attending Universiti Putra Malaysia.

#### **3.4.3 Selection Criteria**

##### **3.4.3.1 Inclusion Criteria**

The inclusion criteria in this study are:

- i. Malaysian citizen.
- ii. Basic skills using digital or computer and internet literate.
- iii. Have good command and understanding of the Malay and English language.

##### **3.4.3.2 Exclusion Criteria**

The exclusion criteria in this study are:

- i. Currently receiving professional assistance for psychiatry diagnosis.
- ii. Current severe self-harm or suicidal ideation.

#### **3.4.4 Sampling Frame**

List of foundation students attending Universiti Putra Malaysia during the recruitment period.

#### **3.4.5 Sampling Unit**

A foundation student attending Universiti Putra Malaysia.

### **3.4.6 Sampling Method**

All the eligible foundation students will be invited to participate in this study. Systematic random sampling will be used to select respondents to be recruited in this study. . Using a sampling interval of 2, every 1 in 2 patients will be selected.

### **3.4.7 Randomization**

Participants who have given consent will be given a unique id number. They will then randomly be allocated to the intervention or control group using their id number. A randomized block design with a block size of four will be used, with the allocation of participants to the group established before the study commenced (Kendall JM, 2003). The randomization will be done by a person who is not a part of the research team, to ensure allocation concealment.

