### **3.4.8 Blinding**

A single blinding will be applied involving the participants. Respondents will not be aware of the intervention allocation, but the researcher and those involved in providing the intervention module will be aware of the allocation. Blinding will be ensured by using an encrypted username for the participants. Participants will also be reminded not to share the content of the intervention.

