**Table 3.1 Summary of Sample Size Calculation**

| Reference
s                     | Mean (sd)
interventi
on group | N
interventi
on group | Mean
control
group | N control
group | Sp   | n1 |
|------------------------------------|-------------------------------------|-----------------------------|--------------------------|--------------------|------|----|
| Campos
et al.,
2018 | 75.91
(8.13)                     | 239                         | 69.02
(8.23)          | 263                | 8.18 | 44 |

The total sample size in ( $n_1$ ) in this study is 88 (44 participants per arm). After considering 50% loss to follow up, a final sample size of 132 (66 participants per arm) was determined to be sufficient for this study.

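### A fixed, disclosed block size of four makes on average one third of assignments predictable if students are allocated as they consent, and the plan does not rule this out

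*Combined protocol and SAP*

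**What the plan says.** Section 3.4.7 gives each consenting student an ID number and allocates by that number: "A randomized block design with a block size of four will be used". The sequence is drawn up in advance of the trial. The section names one safeguard: "The randomization will be done by a person who is not a part of the research team, to ensure allocation concealment". No other block size, variation in size or stratification is mentioned.

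Section 3.4.8 blinds participants only; "the researcher and those involved in providing the intervention module will be aware of the allocation". It does not say when they become aware.

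On order, section 3.3 says "Participants who consented to join the study will then be randomized to either the intervention or control group". On selection, section 3.4.6 invites all eligible students and adds that "Systematic random sampling will be used to select respondents to be recruited in this study", with an interval of 2. The text under Table 3.1 sets the target: "a final sample size of 132 (66 participants per arm) was determined to be sufficient for this study".

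The plan is silent on four things: whether allocation is one by one or for the whole cohort, when each allocation is released, whether IDs follow consent order, and whether those who enrol students see earlier allocations.

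**The concern.** Concealment has two parts. The list must be hidden, and the next entry must not be deducible from what is already known. Section 3.4.7 deals with the first. For the second, the block size is printed in the protocol and does not vary, and there is one site. Anyone who knows the earlier assignments and the position in the block can work out some of the later ones before deciding who is eligible or when to take consent and issue an ID.

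What is at stake is selective enrolment, for example of keener students into the website arm. Both outcomes come from self-administered questionnaires (section 3.7.1). The covariates for adjustment are socio-demographic: age, gender, ethnicity and household income (section 3.5.3). Motivation is not measured, so an imbalance in it would not be corrected by the planned GEE model.

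**Working it through.** The plan gives no figure for predictability, so there is none to reproduce.

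**Inputs**
- Block size 4, fixed (section 3.4.7).
- Allocation 1:1, hence two of each arm per block. The ratio is not stated in section 3.4.7; it is inferred from 66 per arm.
- Total 132 (text under Table 3.1), so 132 / 4 = 33 blocks.
- Assumed, not stated in the plan: allocation proceeds one student at a time while others are still unenrolled, earlier allocations are known to those enrolling, and ID order (hence block position) is known.

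**Step 1: assignments that are certain.** An assignment is certain once one arm is used up within the block. Across the six equally likely blocks:

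| Block | Certain assignments |
|---|---|
| AABB | 2 |
| ABAB | 1 |
| ABBA | 1 |
| BBAA | 2 |
| BABA | 1 |
| BAAB | 1 |

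The mean is 8/6 = 4/3 per block, and (4/3)/4 = 33.3%. By position the probabilities are 0, 0, 1/3 and 1.

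**Step 2: scale to the trial.** The expected count is 33 × 4/3 = 44 of 132. The fourth position is always certain, so at least 33 (25%) are guaranteed. The count is distributed as 33 + Binomial(33, 1/3), with a 95% range of 39 to 49 (29.5% to 37.1%).

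**Step 3: guess rate.** Always guessing the arm with more places left is right with probability 1/2, 2/3, 2/3 and 1 at the four positions. The third is (1/3)(1) + (2/3)(1/2) = 2/3. The sum is 17/6, and (17/6)/4 = 70.8%, against 50% by chance.

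**Step 4: alternatives.**
- *One run after enrolment closes.* Nothing has been released while students are being enrolled, so 0% is certain and the guess rate is 50%.
- *Random blocks of 4, 6 and 8 (equally likely), block starts known but lengths not.* Certainty can arise only in blocks of eight, because in a shorter block a length of eight always leaves both arms open. A block of eight yields 8 × 20% = 1.6 certain assignments on average. Over one block of each size this is 1.6/(4 + 6 + 8) = 8.9%.
- *The same mix, block boundaries unknown.* Simulation over 132 assignments gives about 2% certain and a guess rate of about 68%, guessing the arm with fewer so far.

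**The case against.** The strongest reply is that the prediction needs three conditions the documents never state: one-by-one allocation during recruitment, earlier allocations reaching the enrollers in that period, and a known ID order. Sections 3.3 and 3.4.7 put consent before randomisation, which is equally compatible with allocating the whole consented cohort together, and then nothing is predictable before enrolment. Section 3.4.8 gives no timing for the researcher's awareness and does not say that this person enrols students. This stands. A reader might infer that one third of assignments will in fact be known before each next student is enrolled; the documents do not support that.

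Second, systematic selection of every second student limits choice over whom to approach. This stands in part. Eligibility still turns on judgement (digital skills, command of two languages, section 3.4.3.1), and the timing of consent and ID issue is open. Section 3.4.6 also leaves unclear how inviting all eligible students fits with selecting one in two.

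Third, fixed blocks of four run by an outsider are a legitimate design choice, and no bias in the literacy score has been quantified. Both are true. The outsider nonetheless does not by himself or herself deliver the concealment that section 3.4.7 claims.

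**Conclusion.** The point holds in conditional form. If allocation is sequential and those enrolling know earlier allocations and ID order, a fixed block of four makes on average 33.3% of assignments certain (44 of 132; 95% range 39 to 49; at least 33) and allows 70.8% correct guessing. One third is an expectation; only one quarter is guaranteed. If the whole cohort is allocated together, the figure is zero.

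The plan neither states nor excludes the sequential case. Two further readings would go too far: that concealment has been shown to fail, and that the treatment effect would be biased by a known amount. The conclusion is that the stated safeguard is incomplete and that a better procedure is available at little cost.

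**What to change.** In section 3.4.7, replace the fixed-block sentence with wording such as: *After recruitment closes and baseline questionnaires are submitted, the independent person randomises all consented IDs 1:1 in one run; no allocation is released before then.* Align section 3.3, which mentions randomisation before the baseline measurement, and state in section 3.4.8 when the researcher learns allocations. The cost is protocol wording, a different list-generation setting, and a wait for early consenters until a common start.

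If recruitment must be staggered, use randomly varying block sizes (for example 4, 6 and 8), withhold the sizes from the research team, and keep earlier allocations from those who enrol students. Because varying the blocks lowers the guess rate so little (70.8% to about 68%), the single run is preferred, and under the fallback the withholding of earlier allocations is essential.
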